### Statistical analysis

2.10

Demographic characteristics, general situations, and baseline conditions of the two groups will be compared and analyzed. For measurement data, an independent samples t-test or Wilcoxon rank-sum test will be employed, while χ^2^ test or Fisher test will be used for categorical data.

The incidence of PUR will be accurately assessed using Fisher’s exact test, and the relative risk (RR) along with the corresponding 95% confidence interval will be calculated. For other ordinal data, the Wilcoxon rank-sum test will be applied, while clinical counting data will undergo testing through the χ2 test. Postpartum depression and anxiety will be compared using Fisher’s exact test, and the RR along with the corresponding 95% confidence interval will be computed. Subject blinding effectiveness will be analyzed using the James Blinding Index. All statistical tests will be two-sided, and a *p* value less than 0.05 will be considered statistically significant for the tested differences.

For exploratory subgroup analysis, participants will be stratified into different subgroups based on age (< 40 years, ≥ 40 years), BMI (< 25 kg/m^2^, ≥ 25 kg/m^2^), duration of labor (< 700 min, ≥ 700 min), epidural anesthesia (with or without), vaginal midwifery techniques (forceps midwifery, fetal head attraction midwifery, fetal head rotation, perineotomy), gestational age (> 280 days, ≤ 280 days), and newborn birth weight (< 4,000 g, ≥ 4,000 g). The incidence difference between the two groups will be compared within each subgroup using the same statistical methods as mentioned above.

The primary analysis will follow the intention-to-treat (ITT) principle. Missing data will be handled using multiple imputation. A logistic regression model adjusting for study center will be used for the primary outcome. Secondary and subgroup analyses will apply Bonferroni correction for multiple comparisons.

GraphPad Prism 10.2 will be used for all statistical analysis.

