### Randomization and blinding

2.3

This study will use the network-based clinical trial public management platform (ResMan, http://www.medresman.org.cn/login.aspx) to implement centralized randomization. Randomization will be carried out using stratified block randomization (with block sizes of 4 or 6) according to the four participating research centers, and allocation concealment will be achieved through the central randomization system of the ResMan platform. After patients complete baseline assessments and are confirmed to be eligible, independent researchers will log into the system to obtain an unpredictable, automatically generated random allocation sequence. Group allocation information will be blinded to the study participants, outcome assessors (including personnel who perform BVI-9400 bladder scans, EPDS scoring, and other questionnaire assessments), and data analysts. To maintain blinding consistently across all study centers, these assessors will not be involved in any treatment-related activities and will receive standardized training on blinded assessment procedures. Furthermore, data entry will be performed by independent personnel who are not involved in patient recruitment or treatment delivery. The sham procedure uses non-penetrating needles and 0 mA current to mimic active treatment without physiological effects. At the end of the trial, the James Blinding Index will be used to quantitatively analyze the success degree of blinding. However, due to operational requirements, acupuncture therapists cannot be blinded.

After the final acupuncture treatment, all patients will be asked, “Do you believe that acupuncture has penetrated the skin?” The response will be categorized into three options:Acupuncture penetrated the skin;Acupuncture did not penetrate the skin;I do not know.

This will be taken into consideration to evaluate the success of blinding.

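### Secondary outcomes get unadjusted rank, chi-square and Fisher tests that leave out centre, and the ordinal and count outcomes have no effect estimate that could be reported or pooled directly

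*Protocol article*

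**What the plan says.** All the analysis statements are in section 2.10 of the protocol article.

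- Ordinal outcomes: "For other ordinal data, the Wilcoxon rank-sum test will be applied". No effect measure is given.
- Counts: "while clinical counting data will undergo testing through the χ2 test". Again no effect measure is given.
- Depression: "Postpartum depression and anxiety will be compared using Fisher’s exact test", "and the RR along with the corresponding 95% confidence interval will be computed".
- Continuous data: "For measurement data, an independent samples t-test or Wilcoxon rank-sum test will be employed". This sentence stands in the paragraph on baseline comparisons. That it also governs continuous secondary outcomes is an inference.
- Missing data: "Missing data will be handled using multiple imputation". No outcomes are named.
- Centre: "A logistic regression model adjusting for study center will be used for the primary outcome". No other outcome is given a centre-adjusted analysis.

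Section 2.3 stratifies the block randomisation "according to the four participating research centers".

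**The concern.** Two choices in the same section fit poorly together. The design uses centre as a stratification factor, and the primary analysis respects that, but none of the tests named for the secondary outcomes can take a covariate. Where centres differ in outcome level, an analysis that leaves out centre does not match the design and usually loses some precision.

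The tests named for the ordinal and count outcomes also stop at a p-value. The 0/2/4/6 urination scale (sections 2.5.2.1 and 2.6.1) and the effective rate of urination (section 2.5.2.2) would be reported without a stated effect size and interval. If the multiple-imputation sentence is meant to cover them, the analyst has no estimate and variance to combine across imputed data sets and must choose a pooling method that the plan does not name. For depression there is an estimate, but the p-value comes from a different procedure than the interval, so the two can point in different directions.

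**Working it through.** The plan states no figure on this point, so there is none to reproduce. The check has three parts.

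**1. What each named analysis supplies.** With m imputed data sets, Rubin's rules combine estimates q_i and variances U_i: pooled estimate = mean(q_i), total variance T = mean(U_i) + (1 + 1/m)·B, where B is the variance of the q_i between data sets.

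| Outcome type | Named test | Estimate and variance named? | Centre used? |
|---|---|---|---|
| Primary (PUR) | Fisher with RR; logistic model | yes | yes, in the logistic model |
| Depression (EPDS ≥13) | Fisher | yes, RR with 95% CI | no |
| Counts, such as effective rate | chi-square | no | no |
| Ordinal, such as urination scale | Wilcoxon | no | no |
| Continuous, if the baseline sentence applies | t-test or Wilcoxon | difference and SE from the t-test; none named with Wilcoxon | no |

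The gap in direct pooling is therefore confined to the ordinal and count rows, and to any continuous outcome sent to Wilcoxon. The gap in centre adjustment covers every secondary row. Section 2.5.2.4 (24 h bleeding) also promises adjustment for co-interventions, which none of these tests can deliver.

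**2. Fisher beside an RR interval.** Take 330 per arm (section 2.9), with assumed counts of 33 and 50 events.

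- RR = (33/330)/(50/330) = 0.66; log RR = −0.4155.
- SE = √(1/33 + 1/50 − 2/330) = √0.04424 = 0.2103.
- 95% CI = exp(−0.4155 ± 1.96 × 0.2103) = 0.437 to 0.997, which excludes 1.
- Fisher's exact two-sided p = 0.060, which is above 0.05.

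The same data would be reported as non-significant by the test and as excluding no effect by the interval. This happens only near the boundary, and imputation is not needed for it to occur.

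**3. Does imputation fail with these tests?** A simulation under no treatment effect used these inputs:

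- from the protocol: 330 per arm, four centres, a four-level ordinal outcome, and about 10% missing (section 2.6.2 aims for at least 90% retention);
- assumed: centres differing in outcome level, missingness of 5% in two centres and 15% in the other two, imputation within arm and centre, m = 20, 2,000 runs.

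Centre was left out of every analysis. Log RR, the Mann-Whitney probability θ = P(X<Y) + ½P(X=Y), and the mean difference were pooled by Rubin's rules. The chi-square and rank statistics w_i were pooled by the D2 rule: D2 = [mean(w_i) − ((m+1)/(m−1))·r]/(1 + r), with r = (1 + 1/m)·var(√w_i).

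Type I error at nominal two-sided 5% (Monte Carlo SE √(0.05 × 0.95/2000) = 0.5 points):

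| Pooled analysis | Type I error |
|---|---|
| log RR, Rubin | 4.4% |
| chi-square, D2 | 4.6% |
| Mann-Whitney probability, Rubin | 4.8% |
| rank statistic, D2 | 4.7% |
| mean difference, Rubin | 4.9% |

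Further runs (6,000 each, Monte Carlo SE about 0.3 points) used values missing completely at random, a 15% event rate and scale probabilities of 0.02/0.10/0.28/0.60. The Mann-Whitney probability pooled by Rubin's rules gave 5.4% at 10% missing and 4.9% at 20%. Pooled log RR gave 5.0% and 4.8% in one run and 5.1% and 5.6% in another. All are close to 5%.

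**The case against.** The strongest reply is that little here is wrong. The imputation sentence stands between the intention-to-treat statement and the primary-outcome model, so it may concern the primary outcome only. Its scope and the pooling rule commonly sit in an analysis plan, which is not shown. Rank and chi-square tests on secondary outcomes are conventional. Much of this stands: a missing pooling rule is no finding, and the pooling part of the point is conditional on imputation reaching these outcomes. What remains is what section 2.10 itself fixes, namely tests without centre after centre-stratified randomisation, and no effect measure for ordinal and count outcomes.

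Two stronger readings are tempting, and the document supports neither.

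- A reader might infer that multiple imputation cannot be validly combined with these tests. Depression has a stated RR that pools on the log scale, and D2 and rank-effect pooling serve the chi-square and Wilcoxon tests. Leaving centre out of the analysis does not by itself invalidate imputation.
- A reader might infer an inflated error rate. Simulation can produce one: Wilcoxon on a single completed data set gives 7.4% to 8.1% at 10% missing and 10.1% to 11.4% at 20%. But that is single imputation, and the plan says multiple. Taking the median p-value over imputations also inflates Wilcoxon (6.2% to 6.8% at 10% missing), but the plan names no such rule. The 20% figures exceed the 10% dropout planned in section 2.9.

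**Conclusion.** The point holds as a minor one. The named secondary analyses do not use the factor by which randomisation was stratified. For ordinal and count outcomes they yield no stated estimate with interval, and so nothing that pools directly by Rubin's rules if imputation extends to them. For depression, p-value and interval can disagree near the 5% boundary. No error-rate inflation is claimed: with proper pooling, type I error stayed between 4.4% and 5.6% across the runs shown.

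This rests on the assumed outcome distributions, centre differences and missingness patterns, and on section 2.10 describing the intended secondary analyses in full. The precision lost by omitting centre cannot be sized, because the protocol gives no centre-level outcome data. The simulation does not measure it either, since its allocation was not stratified. Severity is limited because only secondary outcomes are affected.

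**What to change.** For each secondary outcome, take the effect estimate, 95% CI and p-value from one model with arm and centre:

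- EPDS ≥13 and effective rate of urination: logistic or modified Poisson regression;
- the 0/2/4/6 urination scale: proportional-odds regression;
- times, volumes and scores: linear regression, log-transformed if skewed.

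State which outcomes are imputed, and pool the arm coefficient by Rubin's rules for those. Keep the Wilcoxon, chi-square and Fisher tests as observed-case sensitivity analyses. The same models can carry the co-intervention adjustment promised in section 2.5.2.4.

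The cost is analysis-plan wording and modest programming, with no change to data collection or sample size. The downside is that model assumptions, proportional odds in particular, need a check and a stated fallback.

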#### Primary outcome

2.5.1

The primary outcome is the PUR incidence.

The incidence of postpartum urinary retention (PUR) will be evaluated in accordance with the following criteria, which are grounded in the diagnostic guidelines outlined in “Postpartum urinary retention: an expert review” published in the American Journal of Obstetrics and Gynecology.Overt PUR: Inability to void spontaneously within 6 h postpartum or within 6 h after removal of the indwelling catheter following cesarean section.Covert PUR: Post-void residual (PVR) urine volume ≥ 150 mL after spontaneous voiding.Persistent PUR: Requirement for an indwelling catheter or intermittent catheterization by the 3rd day postpartum.

Assessment time points are: the first urination after delivery, 6 h after delivery, the initial urination on the first day, and the second day following acupuncture. Meeting any of the aforementioned criteria at any assessment point will be considered as a positive PUR case.

The PVR of the bladder will be measured using an Ultrasonic Bladder Scanner (BVI-9400 BladderScan^®^, Verathon Medical Europe, Ijsselstein, The Netherlands). All BladderScan BVI-9400 devices will be calibrated annually according to the manufacturer’s guidelines. Operators must complete a standardized training program and pass a competency assessment before performing study measurements. To ensure accuracy, any PVR measurement ≥150 mL will be immediately rechecked by a second, blinded operator within 15 min. The average of the two readings will be recorded as the final PVR value. The recorded PVR of the bladder and whether catheterization was required will be documented. The specific measurement times are illustrated in Figure 3.

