### Sample size

2.9

This study employs a superiority design to evaluate the effect of electroacupuncture on the overall incidence of postpartum urinary retention (PUR), encompassing all subtypes (overt, covert, and persistent). Based on the research findings, the incidence of overt PUR in the intervention group is projected at 4.0%, while in the control group, it is estimated to be 9.0% based on previous observational data and a recent clinical trial in a similar population (4). The non-inferiority margin (*δ*) was set at 5%. Assuming a 1:1 ratio between the intervention and control groups, and utilizing a superiority test with a significance level (*α*) of 0.05, a power (1-*β*) of 80%, and accounting for a potential dropout rate of 10%, the study is planned to enroll 660 patients, evenly distributed with 330 in each group. The calculation formula is as follows:
$$n1=n2=[p_{1}(1-p_{1})+p_{2}(1-p_{2})]{\left(\frac{z_{1-\alpha }+z_{1-\beta }}{p_{1}-p_{2}-\delta }\right)}^{2}$$

While acknowledging that the initial effect size estimation was primarily informed by overt PUR data, we have implemented a comprehensive data collection system to capture all PUR subtypes, ensuring the primary outcome measure “PUR incidence” accurately reflects clinical reality. We anticipate this sample size will provide sufficient statistical power to detect clinically meaningful differences in overall PUR incidence across all subtypes. During final analysis, we will calibrate the effect size according to the actual observed incidence rates of all PUR subtypes, thereby ensuring proper alignment between the effect size and primary endpoint while enhancing the robustness and generalizability of our findings.

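### Section 2.10 gives the primary outcome two unranked analyses, Fisher's exact test with a relative risk and a centre-adjusted logistic regression, and does not say which one decides the trial

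*Protocol article*

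**What the plan says.** The section on the primary outcome (2.5.1) is plain: "The primary outcome is the PUR incidence". A woman is a case if she meets the overt, covert or persistent definition at any assessment, so the endpoint is binary.

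Section 2.10 then gives two analyses of it.

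- Second paragraph (quoted without the last two words of the sentence): "The incidence of PUR will be accurately assessed using Fisher’s exact test, and the relative risk (RR) along with the corresponding 95% confidence interval will". No centre term or stratification is mentioned.
- Fourth paragraph, after the statements on ITT and multiple imputation: "A logistic regression model adjusting for study center will be used for the primary outcome". No effect measure is named for this model.

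The threshold is common to both: "All statistical tests will be two-sided, and a *p* value less than 0.05 will be considered statistically significant".

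On allocation, section 2.3 says: "Randomization will be carried out using stratified block randomization (with block sizes of 4 or 6) according to the four participating research centers".

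For subgroups, section 2.10 says: "The incidence difference between the two groups will be compared within each subgroup using the same statistical methods". It calls these analyses exploratory and puts them under a Bonferroni correction.

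**The concern.** A confirmatory trial needs one test that decides the primary hypothesis. Here two tests are attached to the same endpoint, and neither is labelled decisive, supportive or a sensitivity analysis. They can disagree, and the choice could then be made after the results are known. The effect scale is open as well: the relative risk is tied to Fisher's test, while a logistic model naturally yields an odds ratio.

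Fisher's test also sits badly with the rest of the plan. It takes no account of the centre strata used in randomisation. It returns a p-value without an estimate and variance to combine, so there is no standard way to pool it over the planned imputations. The subgroup analyses inherit the ambiguity, and testing each level separately does not show whether the effect differs between levels.

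**Working it through.** **Inputs from the protocol article.** Rates of overt PUR 4.0% (EA) and 9.0% (sham), 330 per arm, 10% dropout (330 × 0.9 = 297), power 80% (all section 2.9); two-sided 0.05 (section 2.10); four centres (section 2.3). **Assumed:** centre-specific rates and overall PUR rates, which the article does not give.

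**1. The planned sample size.** With δ left out and a one-sided α of 0.05, the printed formula gives [0.04×0.96 + 0.09×0.91] × ((1.645 + 0.842)/0.05)² = 0.1203 × 2473 = 297.5, so 298 per arm. That becomes 332 (÷0.9) or 328 (×1.1). The pooled-variance version gives 300, and 300 × 1.1 = 330. The stated 330 is thus reproduced, so 330 and 297 are the relevant sizes.

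**2. The two analyses can disagree on the same data.** Take 14/330 (EA) against 27/330 (sham), without a centre term.

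- Fisher's exact test, two-sided: p = 0.052.
- Logistic regression: OR = (14×303)/(27×316) = 0.497; ln OR = −0.699; SE = √(1/14 + 1/316 + 1/27 + 1/303) = 0.339; z = −2.06; p = 0.039.
- RR = 14/27 = 0.519.

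One analysis is negative and the other positive.

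**3. Power by exact enumeration of two binomials, two-sided 0.05** (losses from unrounded values):

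| Per arm | EA vs sham | Fisher | Pearson | Loss (points) |
|---|---|---|---|---|
| 330 | 4% vs 9% | 69.8% | 75.3% | 5.5 |
| 297 | 4% vs 9% | 64.5% | 71.3% | 6.8 |
| 330 | 10% vs 17% (assumed) | 71.9% | 75.3% | 3.5 |
| 297 | 10% vs 17% (assumed) | 66.7% | 71.0% | 4.3 |
| 330 | 20% vs 30% (assumed) | 82.4% | 84.6% | 2.1 |
| 297 | 20% vs 30% (assumed) | 78.0% | 80.8% | 2.7 |

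At 330 per arm, Fisher's true size is 3.4% at a common rate of 6.5% and 3.6% at 9%. Pearson's is 5.0% and 4.9%.

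**4. Centre-adjusted logistic regression by simulation.** 6,000 trials per setting, four equal centres, a common odds ratio, and an assumed between-centre SD on the logit scale of 0, 0.3, 0.6 or 1.0.

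- Power at 330 per arm: Wald 74.4-75.9%, likelihood ratio 76.0-76.8%.
- Power at 297 per arm, SD 0 to 0.6: Wald 69.5-71.2%, likelihood ratio 71.3-72.7%.
- Fisher and Wald give opposite verdicts in about 5-6% of trials at 4% vs 9%, and in up to about 8% with SD 1.0 at 297 per arm.

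**5. Where the loss comes from.** The Pearson test in step 3 has no centre term either, yet Fisher loses 5.5 to 6.8 points to it. Comparing the stratified Mantel-Haenszel test with pooled Pearson isolates the effect of centre. At 297 per arm the powers are 71.2% and 71.4% with no centre differences, and 73.6% and 72.5% with SD 1.0. Omitting centre therefore costs about one point even in the extreme case.

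**6. Effect scale.** At 4% vs 9%, RR = 0.04/0.09 = 0.44 and OR = (0.04/0.96)/(0.09/0.91) = 0.42.

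**The case against.** The best reply is that the plan does point to one analysis. The logistic sentence stands in the paragraph that describes the primary analysis, next to ITT and multiple imputation, and the model matches the stratified randomisation. Fisher's test with a relative risk could then be read as an unadjusted summary. This has weight: it is too strong to say that nothing links the model to the primary analysis. But the ITT sentence fixes only the population, and the only effect measure named for PUR belongs to the other paragraph. A separate analysis plan might rank the two, but the article itself states both, so this is more than a detail left out.

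Four stronger inferences are tempting and are not supported.

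- *The power loss comes from ignoring the strata.* Step 5 shows otherwise.
- *Two tests inflate the false-positive rate.* Under the null with no centre differences at 330 per arm, the simulation rejects in 3.62% (Fisher) and 4.98% (Wald) and they disagree in 1.37%. Either test rejects in (3.62 + 4.98 + 1.37)/2 = 4.99%. Fisher's rejections lie almost wholly inside those of the Wald test.
- *The two effect scales differ greatly.* At the protocol's rates, 0.42 and 0.44 are close. They separate only if PUR is commoner, and the odds ratio is itself an inference because the article does not name it.
- *Subgroup false positives are uncontrolled.* The plan calls these analyses exploratory and corrects them by Bonferroni. What remains is that a corrected within-level test is still not a test of interaction.

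**Conclusion.** The contradiction is real and should be removed before unblinding: one primary outcome has two unranked tests and an open effect scale. What is at stake is whether a borderline result counts as positive. At 4% against 9% that affects about 5-6% of trials. Choosing Fisher's test would cost about 5-7 points of power through its conservatism.

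These figures rest on overt-PUR rates, while the endpoint covers all subtypes. If overall PUR is commoner, the loss is about 3.5-4.5 points at an assumed 10% vs 17% and 2-3 points at 20% vs 30%. The logistic results also assume equal centres and a common odds ratio. Power is below 80% for either test at 4% vs 9%, because the sample size formula uses a one-sided α and the analysis is two-sided; that is a separate matter. The subgroup point is secondary.

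**What to change.** In section 2.10, or an amendment to it:

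1. State that the primary analysis is the logistic regression of PUR on arm and centre in the ITT set, pooled over the imputations, and that its p-value alone decides the primary hypothesis.
2. Name one effect scale consistent with the planned relative risk, for example a standardised RR with 95% CI from that model.
3. Label Fisher's exact test as supportive.
4. For the exploratory subgroups, add the arm-by-factor interaction test from the same model and show the RR and CI within each level descriptively.

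The cost is a few sentences and a little more analysis work. No new data are needed, and neither the sample size nor the conduct of the trial changes.

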#### Electro-acupuncture group

2.4.1

The selected acupoints will include Baihui (GV20), Zhongji (CV3), and Guanyuan (CV4), adhering strictly to the National Acupoint Standard of the People’s Republic of China in 2021 (GB/T 12346–2021). The first treatment session will be initiated within 1 h postpartum (±30 min). Detailed positioning is illustrated in Table 2 and Figure 2. Patients will be positioned supine during the procedure. Adhesive pads will be applied to the skin over the acupoints, followed by the insertion of single-use acupuncture needles (0.25 mm * 40 mm, Hwato, Suzhou, China) through the adhesive pads.

**Table 2 tab2:** Locations and needling methods of acupoints for electro-acupuncture group.

Acupoint	Location	Needling method
Baihui (GV20)	On the head, 5 inches above the center of the front hairline.	Depth of 10-15 mm and an angle parallel to the scalp, then adopt the method of small amplitude and high frequency twisting(the range of twirling of the needle was 90°- 180°, and the frequency was 100 to 120 times a minute) for 1 min.
Zhongji (CV3)	In the lower abdomen, 4 cun below the umbilicus, on the anterior median line.	Obliquely acupunctured 10-20 mm and at a 45° angle to the abdomen.
Guanyuan (CV4)	In the lower abdomen, 3 cun below the umbilicus, on the anterior median line.	Obliquely acupunctured 10-20 mm and at a 45° angle to the abdomen.

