### Outcome measurements

2.5

At the baseline, clinical and sociodemographic data will be collected from all patients, encompassing:(1) Basic Information:Age;Gestational age at delivery;Height;Weight (Predelivery);Body Mass Index (Predelivery);Conception mode.(2) Management of the Delivery Process:Duration of labor;Use of epidural anesthesia;Incidence of episiotomy and perineal lacerations;Instances of vacuum-assisted and instrumental delivery;Process of placental delivery;Administration of uterine contractile drugs.(3) Newborn Condition:Weight;Length;Apgar score.

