##### Cumulative amount of 24 h postpartum bleeding

2.5.2.4

The volume of vaginal bleeding within the first 24 h after delivery will be documented using postpartum measuring pads. These pads will be changed regularly every 2–4 h, and upon replacement, they will be weighed and measured, with the unit of measurement being milliliters (“mL”). Blood loss will be measured using pre-weighed pads changed every 2–4 h, with volume (mL) calculated as weight difference (g) × 1.06 (density conversion factor). Permitted co-interventions include uterotonics (e.g., oxytocin) but exclude prophylactic catheterization. All co-interventions will be recorded and adjusted for in the analyses.

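### The primary model adjusts for centre alone, which is valid, but makes no use of delivery factors already collected as baseline data; a short prespecified covariate list would add a little power

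*Protocol article*

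**What the plan says.** For the primary outcome, section 2.10 (Statistical analysis) states: "A logistic regression model adjusting for study center will be used for the primary outcome". No other covariate is named for that model. Section 2.3 stratifies randomisation by the four centres, so the model matches the design. The same section 2.10 also gives an unadjusted analysis of the same outcome, in a sentence that opens: "The incidence of PUR will be accurately assessed using Fisher’s exact test, and the relative risk (RR) along with the corresponding 95% confidence interval will".

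Section 2.5 (Outcome measurements) introduces its list with "At the baseline, clinical and sociodemographic data will be collected from all patients". The list includes "Duration of labor;Use of epidural anesthesia;Incidence of episiotomy and perineal lacerations;Instances of vacuum-assisted and instrumental delivery". Section 2.4.1 places treatment after delivery: "The first treatment session will be initiated within 1 h postpartum (±30 min"). Section 2.10 uses labour duration, epidural and assisted delivery only to define exploratory subgroups.

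One other sentence bears on adjustment. Under the bleeding outcome (section 2.5.2.4), after naming uterotonics as an example, the protocol says: "All co-interventions will be recorded and adjusted for in the analyses".

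**The concern.** The Discussion attributes PUR to disturbance of muscle or nerve function during childbirth, so the recorded features of labour and delivery are natural candidates for predicting the outcome. If they do predict it, a model that includes them tests the treatment effect with somewhat more power for the same number of women. It also accounts for chance imbalance, from which stratification by centre alone gives no protection. Section 2.10 plans tests of baseline differences but no prespecified response to them, which leaves room for adjustment chosen after the data are seen.

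Power is not plentiful. The sample size reproduces only under a one-sided test, while the analysis is two-sided, so even a small gain at no cost in patients is worth having.

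**Working it through.** **Inputs from the protocol.** Section 2.9: 4.0% versus 9.0% (overt PUR), α 0.05, power 80%, dropout 10%, 330 per group. Section 2.10: two-sided tests.

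**The plan's own figure.** With p₁ = 0.04 and p₂ = 0.09, p₁(1−p₁) + p₂(1−p₂) = 0.0384 + 0.0819 = 0.1203. Section 2.9's formula with δ = 0 and one-sided α gives 0.1203 × ((1.645 + 0.842)/0.05)² = 297.5 per group, and 297.5/0.9 = 330.6. The stated 330 is reproduced on those terms.

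**Power under the planned two-sided test, no covariates.** Power = Φ(0.05/√(0.1203/n) − 1.96).
- n = 297 evaluable per group: Φ(2.484 − 1.96) = 70.0%
- n = 330 per group: Φ(2.619 − 1.96) = 74.5%

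Expected events: 297 × 0.13 = 38.6, or 330 × 0.13 = 42.9. These count overt PUR only. Section 2.5.1 also counts covert and persistent PUR at any assessment, so the total may be larger; the Introduction quotes an incidence range of 1.5% to 45%.

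**Assumptions.** The protocol gives no figure for how strongly any delivery factor predicts PUR, and no rate for overall PUR. Both are assumed: a single prognostic score of three strengths, and an illustrative overall rate of 30% versus 20%.

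**Simulation.** 3,000 trials per scenario, 297 per group, two-sided 0.05, logistic regression with and without the score, centre not simulated. The last column is an analytic check that replaces n by n/(1−R²) in the power formula above. At 30% versus 20% the variance term is 0.21 + 0.16 = 0.37, the difference is 0.10, and power without covariates is 80.9%.

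| Rates | AUC | R² | Simulated power, without → with score | Fall in risk-difference variance | Analytic power, without → with score |
|---|---|---|---|---|---|
| 9% vs 4% | 0.64 | 0.016 | 69.6 → 69.4% | 2% | 70.0 → 70.7% |
| 9% vs 4% | 0.70 | 0.038 | 69.3 → 71.2% | 5% | 70.0 → 71.7% |
| 9% vs 4% | 0.75 | 0.070 | 68.1 → 71.8% | 7% | 70.0 → 73.1% |
| 30% vs 20% | 0.64 | 0.044 | 80.8 → 81.9% | 4% | 80.9 → 82.6% |
| 30% vs 20% | 0.69 | 0.091 | 82.1 → 84.8% | 9% | 80.9 → 84.4% |
| 30% vs 20% | 0.74 | 0.147 | 78.0 → 84.5% | 16% | 80.9 → 86.6% |

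The simulation error of one power figure is about √(0.7 × 0.3/3000) = 0.8 points. The unadjusted figures should agree within each pair of rates, and their spread is noise; the 78.0% is clearly low against 80.9%. The analytic gains, 1 to 3 points at 9% versus 4% and 2 to 6 points at 30% versus 20%, fit the simulated ranges of about 0 to 4 and 1 to 7.

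**A second simulation.** Three binary predictors with assumed odds ratios 2.5, 2.5 and 2.0, and 330 per group:
- 9% vs 4%: 72 → 73%
- 20% vs 13.5%: 63 → 66%
- 30% vs 22.5%: 60 → 63%

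It agrees in direction and size, although it allows for no dropout.

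**Scale.** The mean standard error of the log odds ratio rises slightly with adjustment, for example from 0.367 to 0.381 in the third row. The conditional odds ratio lies further from 1, so power can still rise. The gain in precision belongs to the standardised RR or risk difference.

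**Timing.** The passages point in two directions.
- Section 2.2.1 randomises after consent, and Table 1 puts consent before delivery. Section 2.2.4 keeps women converted to caesarean among the randomised. This suggests randomisation before delivery.
- Section 2.3 randomises after baseline assessments, which section 2.5 says include delivery and newborn data. This suggests randomisation after delivery.

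**The case against.** The strongest reply is that nothing here is wrong. A model that matches the stratification is valid, and a fuller covariate list may stand in the full protocol or an analysis plan not shown. That is right as far as it goes: this is an improvement to a choice the article states, and no defect in that choice is shown.

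A reader might infer more than the documents support:
- **That the primary estimate is biased or its odds ratio needlessly imprecise.** Randomisation protects the centre-only comparison, and adjustment does not reduce the standard error of the log odds ratio.
- **That the delivery factors are safe covariates because they precede session 1.** The time that matters is randomisation. If women are randomised before delivery, these factors arise after randomisation. Section 2.3 blinds participants, outcome assessors and data analysts but does not name delivery staff, so an influence of allocation on delivery care is not excluded.
- **That the gain is large.** Prognostic strength and overall incidence are both assumed. At the protocol's own rates, the weakest assumed score gives no detectable change in simulation, and about 39 to 43 events support only a few covariates.
- **That use as subgroup factors shows prognostic value.** The subgroups are exploratory and look for differences in effect; they do not establish that a factor predicts PUR.
- **That the co-intervention sentence already supplies the adjustment.** It stands under the bleeding outcome and concerns care such as uterotonics. Applied to the primary model, it could bring in variables arising after treatment.

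What remains is that collected data with plausible prognostic value go unused in the primary model, and that a prespecified list costs very little.

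**Conclusion.** The point holds as a modest efficiency suggestion. The expected benefit is about 0 to 4 power points, with 2% to 7% less risk-difference variance, at 9% versus 4%. It is about 1 to 7 points if overall PUR is 20–30%, with 4% to 16% less variance in the 30% versus 20% case. These ranges depend on a prognostic score with AUC of about 0.64 to 0.75, which the protocol neither supports nor rules out.

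It does not repair the larger shortfall nearby: one-sided planning against a two-sided test takes power from 80% to about 70% at 297 per group, more than adjustment would recover. Whether delivery factors may enter the model at all depends on resolving the time of randomisation.

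**What to change.** 1. Reconcile sections 2.2.1, 2.2.4 and Table 1 with sections 2.3 and 2.5 on when randomisation takes place.
2. If it follows delivery, prespecify before unblinding a primary logistic model with centre, epidural (yes/no), instrumental delivery or episiotomy (yes/no) and labour duration.
3. If it precedes delivery, either state that delivery staff do not know the allocation and use the same list, or limit the list to factors fixed before randomisation, such as age and BMI.
4. Report the RR with its 95% confidence interval by standardisation from this model, and keep the centre-only model as a sensitivity analysis.
5. State a coding rule for women converted to caesarean, who stay in the ITT set and for whom episiotomy, instrumental delivery or labour duration may not apply.
6. Add nothing that arises after session 1, and say that the co-intervention sentence in section 2.5.2.4 does not extend the primary model.

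The cost is analysis wording, the coding rule and slightly more analysis work. No extra patients are needed, and the covariates are already collected.
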